### Safety and adverse events

The therapy provider and/or study team will review adverse events of special interest (AESI) at each study visit. Two adverse events of special interests (AESIs) in Common Terminology Criteria for Adverse Events, CTCAE version 5 [63] monitored by the DSMB (Data Safety Monitoring Board) for this trial safety include: weight loss of grade > 2, or aspiration of grade > 2. In addition, at week 6 of RT, the study team will record the onset and peak severity of selected adverse events during RT, also graded using CTCAE version 5, for the following categories: dysphagia, oral and pharyngeal mucositis, oropharyngeal pain, nausea, vomiting and dermatitis. Attribution of each AESI to study intervention will be assessed by the clinician and/or study team according to best clinical judgment. It is expected that many of the AESIs will be related to the RT (cancer treatment). The summaries of AESIs will be reviewed regularly by the trial DSMB.

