#### RE-ACTIVE therapy (arm 1)

Participants will receive no swallowing therapy sessions from the speech language pathologist unless they develop dysphagia. If and when the following signs and symptoms of dysphagia develop, patients will begin RE-ACTIVE therapy as per the same EAT+EXERCISE protocol in Arm 3. The trigger to initiate swallowing intervention was selected based on input from stakeholders including, patients, family members, and a wide array of clinical providers involved in the treatment of HNC patients. Arm 1 participants will “trigger” when any one of the following conditions are met:
Participant reports a common dysphagia symptom (i.e., “choking”) on a standardized PRO screen taken weekly during RT, defined as a score ≥ 6 on the MDASI-HN choke item “difficulty choking on foods or liquids” [33].Participant becomes 100% feeding tube dependent as monitored weekly during RT.Participant develops aspiration pneumonia during RT, as per suspicion by any healthcare team member, that then triggers prescription of an antibiotic.

Participants who develop or endorse any one of the above three trigger conditions will be referred to begin RE-ACTIVE swallowing therapy according to the EAT+EXERCISE model within three RT days of their trigger.

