#### PRO-ACTIVE therapy (arms 2 & 3)

All participants randomized to PRO-ACTIVE arms will receive in person swallowing therapy sessions with a speech language pathologist once before RT begins then every 2 weeks during RT (weeks 2, 4, 6) and coached to continue daily independent therapy in between live sessions. The two PRO-ACTIVE arms will adhere to the same frequency of live sessions but differ in the intensity of the exercise. Specifically,

**PRO-ACTIVE “EAT” (Arm 2)** will aim to keep the patient eating challenging foods safely and efficiently through the duration of RT (typically 6 to 7 weeks). Arm 2 represents a low intensity PRO-ACTIVE therapy, not requiring any additional exercise or therapy outside of mealtime.

In contrast, **PRO-ACTIVE “EAT + EXERCISE” (Arm 3)** will include the same therapy as Arm 2 (EAT) *and in addition,* the patient will be trained in swallowing exercises to be executed independently between meals (EXERCISE). Arm 3 represents a high intensity PRO-ACTIVE therapy asking the patient to perform a standardized set of throat exercises outside of mealtime.

All three swallowing therapy interventions require no training or expertise beyond that of a typical provider, namely a speech language pathologist, in a usual care setting. Each arm represents a reproducible version of therapy options that are currently provided in usual care settings in this population [19, 22]. In keeping with pragmatic trial standards [34], co-interventions are not prohibited (e.g., pain management, other non-swallowing behavioral therapies, other swallowing therapies post RT, or other systemic cancer treatment including chemotherapy and surgeries), but will be tracked in the trial database. Likewise, patients with feeding tube in situ at baseline will not be excluded, but will be tracked in the trial database. For the purpose of reproducibility and understanding natural adherence, patients will be asked to log adherence to their swallowing therapy interventions with a simple paper “diary” log.

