### Outcome measures

This is a pragmatic RCT. Therefore, effectiveness will be assessed through a series of questionnaires and clinical exams to study swallowing status and swallowing-related QOL. A complete list of study activities is summarized in Table 1. The follow-up schedule is carefully planned to align with the schedule of cancer surveillance visits that patients attend in usual practice setting. We will evaluate patients to 12 months to examine long-term effectiveness. Capture of outcome intervals have been set with wide, but discrete windows to enhance flexibility. In all arms, off schedule visits are allowable should problems arise, as per usual care. Clinical testing specified in the protocol represents what is standard at institutions that have adopted the PRO-ACTIVE models as routine care.

**Table 1 Tab1:** PRO-ACTIVE Schedule of Activities

	Pre-RT		During RT						Post-RT	
	Baseline		Week 1 ±3 tx days	Week 2 ±3 tx days	Week 3 ±3 tx days	Week 4 ±3 tx days	Week 5 ±3 tx days	Week 6 ±3 tx days	3 Months ±2 weeks	12 Months ±4 weeks
**Time**	**1**	**2** (randomization to 3 tx days after RT Start)	**3**	**4**	**5**	**6**	**7**	**8**	**9**	**10**

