MDASI-HN is a multi-symptom PRO instrument designed to measure severity or burden of cancer-related symptoms and their interference with or effect on patients’ daily functioning [33, 45]. Symptom burden refers to the severity of physical or mental experience by a patient with a specific symptom. Symptom measures are more specific and direct than QOL measures and thus are more sensitive to treatment-related changes. The 28-item MDASI-HN multi-symptom inventory measures include 13 core items (“systemic symptoms”: pain, fatigue, sleep, etc.), 9 head and neck specific items (“local symptoms”: dry mouth, mucus, shortness of breath, taste, etc.), and 6 interference items (activity, work, relations, etc.). The core MDASI items were validated for use in cancer patient populations regardless of the specific diagnosis or type of therapy [45] and thus can be used to compare symptom burden between different types of cancer. The 9 head and neck specific items were validated internally at MDACC with regard to construct and concurrent validity in a cohort of 205 HNC patients [33]. Internal consistency reliability is high in the core MDASI score, the 9 head and neck-specific items, and the 6 interference items (Cronbach’s α: 0.72–0.92). MDASI-HN can be completed in less than 7 min. MDASI-HN offers quantification of overall symptom burden, but also 2 dysphagia-specific items (“difficulty swallowing”, “choking”) and will be used to understand and adjust for symptoms such as mouth sores, pain, or dry mouth, that make eating challenging during RT. The investigators have experience in using MDASI-HN in weekly radiation clinics for symptom monitoring with a resultant publication characterizing the evolution and cumulative increase in symptoms weekly during HNC RT [46]. Symptom burden can be considered both a secondary outcome, but also a potential confounder (i.e., competing toxicity) that may influence adherence to swallowing therapy.
3)Videofluoroscopic Swallow (VFS) Studies

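### Peak acute toxicity during RT is recorded at week 6, about one treatment week before a 7-week course ends

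*Protocol article*

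**What the plan says.** Three statements in the protocol article bear on this point.

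- Course length. PRO-ACTIVE therapy (arms 2 & 3) describes the EAT intervention as running "through the duration of RT (typically 6 to 7 weeks".
- Toxicity record. Safety and adverse events states: "at week 6 of RT, the study team will record the onset and peak severity of selected adverse events during RT". The categories are dysphagia, oral and pharyngeal mucositis, oropharyngeal pain, nausea, vomiting and dermatitis, graded with CTCAE version 5.
- Schedule. The last during-RT column of Table 1 is headed "Week 6 ±3 tx days". There is no week 7 column. Footnote i moves two entries in the week 6 column, MDADI and the RT plan archive, to the end of RT. It is not attached to AESI, Medical History or the trigger rows.

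On the RE-ACTIVE triggers, the text has the choking item assessed "on a standardized PRO screen taken weekly during RT" and has the tube criterion as "Participant becomes 100% feeding tube dependent as monitored weekly during RT". Table 1 marks Trigger Review and Trigger PRO in weeks 1 to 6.

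**The concern.** The record is meant to hold the worst grade reached during RT, but it is made at a time when a 7-week course is still running. The protocol calls that course length typical, so this is not a rare exception.

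A late peak is plausible on the protocol's own account: Secondary outcomes, under MDASI-HN, cites the investigators' earlier work "characterizing the evolution and cumulative increase in symptoms weekly during HNC RT". If toxicity builds up over the course, the final week is a likely place for the maximum.

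At stake is the completeness of the acute-toxicity description. Peak grades would be understated, and some first onsets missed, in participants with the longest courses. No later entry in Table 1 repairs this. The next scheduled AESI review is at 3 months after RT, and AESIs cover only weight loss and aspiration.

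**Working it through.** The plan states no figure on this point, so there is none to reproduce. The check counts the treatment days left after the record.

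**Inputs**
- Course length: 6 to 7 weeks (PRO-ACTIVE therapy section).
- Time of record: week 6 (Safety and adverse events).
- Window: ±3 treatment days (week 6 column of Table 1). The peak-severity record has no row of its own there, so it is an assumption that this window applies.
- Fractionation is not given. Assumed: 5 fractions a week, so 6 weeks = 30 and 7 weeks = 35 treatment days.
- Nominal visit: last day of week 6, day 30, so the window is days 27 to 33.

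**Formula:** uncovered days = max(0, course length − visit day).

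| Course (fractions) | Visit day 30 | Latest, day 33 | Earliest, day 27 | Share of RT (range) |
|---|---|---|---|---|
| 35 | 35 − 30 = 5 | 35 − 33 = 2 | 35 − 27 = 8 | 14.3% (5.7% to 22.9%) |
| 33 | 33 − 30 = 3 | 33 − 33 = 0 | 33 − 27 = 6 | 9.1% (0% to 18.2%) |
| 30 | 30 − 30 = 0 | 0 | 30 − 27 = 3 | 0% (0% to 10%) |

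For a 35-fraction course the gap stays open even at the latest permitted day. For 31 to 33 fractions it can close, but only if the visit falls late enough in the window.

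**Sensitivity to the assumptions**
- Visit anchored on the first day of week 6 (day 26, window 23 to 29): a 35-fraction course leaves 35 − 26 = 9 days, range 35 − 29 = 6 to 35 − 23 = 12.
- Six fractions a week: 35 fractions finish within week 6 (6 × 6 = 36 treatment days). A visit at the end of that week then leaves 0 days (at most 35 − 33 = 2), so the gap largely closes. This is no longer a course of about 7 weeks.

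**Can week 6 be read as the end of RT?** Footnote i exists because the two times can differ, and the authors used it for two entries in the same column. The Safety section names week 6 without that qualification.

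**Trigger checks, for scale.** Therapy must begin "within three RT days of their trigger", so the last trigger day certain to lead to therapy within RT is course length − 3. For 35 fractions that is day 32. The days after a week 6 check on which a new trigger is still actionable are 32 − 30 = 2 (0 for a check on day 33, 5 for one on day 27). For 33 fractions they are 30 − 30 = 0 (up to 30 − 27 = 3), and for 30 fractions 0. Day 32 already lies inside the week 6 window.

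**The case against.** The strongest reply is that nothing in the plan depends on these grades. They are not among the listed outcomes, they are not the two AESIs that the DSMB monitors, and no described analysis uses them. The timing is the same in all arms. This stands, and it keeps the point minor.

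Second, capture near the end of RT is better than the toxicity record alone suggests. MDADI is completed at the end of RT, Tube PRO every 2 weeks for the first 3 months after it, and complication details are abstracted from the chart. Swallowing-related quality of life and tube use are thus measured soon after week 6. None of these sources is stated to give a CTCAE peak grade for mucositis, pain, nausea, vomiting or dermatitis.

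Third, footnote i cuts both ways: end-of-RT items sit in the week 6 column, so that column also serves as the closing RT visit. A site might therefore make the record late, but the text does not tell it to.

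Fourth, the cited symptom work concerns patient-reported MDASI scores, not CTCAE grades. It makes a late peak plausible without showing how often one occurs. This also stands.

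A reader might infer something stronger: that RE-ACTIVE trigger checks stop at week 6 in conflict with the text, since Outcome measures says "A complete list of study activities is summarized in Table 1". The documents do not support this as an error of consequence. The text gives the rule, weekly during RT, and a missing column is not an instruction to stop. The yield is 0 to 5 actionable days in a 35-fraction course, the pneumonia trigger does not depend on a weekly form, and off-schedule visits are allowed in all arms.

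**Conclusion.** The point holds for courses that run to about 7 weeks. The onset and peak-severity record is made about 5 treatment days before RT ends (2 to 8 with the window), so events that begin or peak after it are missed by this record in all arms. The count rests on 5 fractions a week, 35 fractions, a visit nominally on the last day of week 6, and the Table 1 window applying to this record.

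It should not be widened to every course beyond 6 weeks, since up to about 33 fractions can be covered by the window. Nor should it be read as bias in the treatment comparison: the primary contrast and the sample size are not touched. The frequency of 7-week courses and of last-week peaks is not in the document, so the number of participants affected cannot be stated. The severity is minor. The missing week 7 trigger column is at most a matter of aligning the table with the text, with negligible effect.

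**What to change.** In Safety and adverse events, time the onset and peak-severity record at the end of RT instead of week 6, and tie it to footnote i of Table 1, alongside MDADI. Uncovered days then become course length − course length = 0, whatever the course length or fractionation.

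The cost is a change of wording and of form timing. It adds no visit, because MDADI is already completed at that point and the participant attends for the last fraction in any case.

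Optionally, add a note to the two trigger rows of Table 1 that weekly checks continue until RT ends, so that table and text read alike. If a week 7 check is written in, it should fall by treatment day 32 of a 35-day course; a later one cannot guarantee that therapy starts within RT.

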### Data management plan

The data management plan was developed in accordance with PCORI Methodology Standards for Data Integrity and Rigorous Analysis*.* Data sources include the electronic health record, PRO questionnaires, imaging data (videofluoroscopy and DICOM radiation dose-grids), and study specific questionnaires. A robust centralized web-based database was designed and maintained by the Techna Institute: Health Informatics Core, an independent research institute within UHN. Manuals of Procedures (MOP) will ensure harmonized entry of individual data items from each source and site under a common data model structure. Authentication, anonymization, and confidentiality plans are detailed in the contractual arrangement with the Techna Institute.

### Statistical analysis

#### Primary endpoint

For the primary endpoint, an intention-to-treat (ITT) approach will be applied incorporating a gate-keeper method to control risk of Type 1 error in the setting of multiple comparisons [64, 65]. The primary hypothesis (Hyp 1.1) is that the combined PRO-ACTIVE interventions (PRO-ACTIVE EAT and PRO-ACTIVE EAT+EXERCISE) will result in a better swallow outcome compared to RE-ACTIVE as measured by duration of feeding tube use in the first year after the completion of RT. If PRO-ACTIVE is superior in Hyp 1.1, we will assess the dose response of the PRO-ACTIVE arms. The secondary hypothesis (Hyp 1.2) is that the most intensive intervention (PRO-ACTIVE EAT+EXERCISE) will be more effective than the least intensive (PRO-ACTIVE EAT).

The initial analysis will compare the RE-ACTIVE group to the combined PRO-ACTIVE groups in terms of the duration of feeding tube use operationalized as count of days of tube use from end of RT to last tube use within the 12-month study period by means of a multiple linear regression model with covariate adjustment. The presence of a feeding tube which is not being used for feeds is disregarded. The treatment effect will be expressed as absolute mean difference along with 95% confidence intervals. If this test yields *p* < 0.05, the two PRO-ACTIVE groups (EAT versus EAT+EXERCISE) will be compared using the same linear analysis method. The meaningful variables we will include in the regression model are: age (as a continuous variable); HPV status (oropharyngeal site vs all others); surgery (yes/no); chemotherapy (yes/no); radiation dose (as a continuous variable); and, facility (as a categorical variable to account for practice variation across the eleven sites).

The largest threat of missing data is non-random loss of outcomes data for the primary endpoint. Missing data for the primary endpoint is extremely unlikely because it is a simple variable that can be ascertained in clinic or remotely via telephone/web interview of the patient. Non-random missing data is more likely for outcomes requiring clinic examination (i.e., videofluoroscopy) for which we have estimated attrition at 26% based on prior longitudinal work from the investigators [38]. For outcomes missing in > 10% of patients, we will consider multiple approaches. One method we may employ is inverse probability weighting approach to account for statistical uncertainty due to missingness. Another option we will explore is multivariate imputation using chained equations [66]. When similar inferences are derived from complete case analysis and imputation, we will report complete case analysis results for simplicity and transparency.

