## Aims and hypotheses

To address this evidence gap, the primary aim (Aim 1) of the PRO-ACTIVE trial is to compare the effectiveness of PRO-ACTIVE versus RE-ACTIVE swallowing interventions among patients with HNC planned to undergo RT. We hypothesize that at 12-months post radiotherapy the combined PRO-ACTIVE therapies are more effective than RE-ACTIVE therapy (Hyp 1.1); and, if so, that more intensive PRO-ACTIVE (EAT + EXERCISE) is superior to less intensive PRO-ACTIVE (EAT) (Hyp 1.2). Effectiveness will be measured based on reduced duration of feeding tube dependency, a pragmatic outcome valued by diverse stakeholders including patients, caregivers and clinicians [13, 21, 25, 26].

The second aim (Aim 2) of the PRO-ACTIVE trial is to compare the relative benefit or harm of PRO-ACTIVE to RE-ACTIVE swallowing intervention on all secondary outcomes at both 3- and 12- months post radiotherapy, namely: swallowing impairment, maximum interincisal opening (trismus), swallowing-related QOL, symptom burden, self-reported pneumonia, malnutrition and mood disorder, cancer coping strategies, diet level, feeding tube rates, weight loss, hospitalization and/or emergency department (ED) presentation. In addition, the second aim will compare the benefit on reduced duration of feeding tube presence at 3-month post radiotherapy. Our hypothesis for this second aim is that the combined PRO-ACTIVE interventions will result in better secondary outcomes at 3- and 12- months following the completion of RT (Hyp 2.1). As in our primary aim, for each secondary outcome for which PRO-ACTIVE is superior, dose response of the PRO-ACTIVE arms will be examined hypothesizing the more intensive therapy as superior (Hyp 2.2).

The third aim (Aim 3) of the PRO-ACTIVE trial is to explore the relative benefit or harm of the PRO-ACTIVE and RE-ACTIVE swallowing interventions in relevant subgroups according to the following: age, tumor site, prior surgery, radiation dose, chemotherapy use, and prophylactic feeding tube use. Our hypothesis for this third aim is that all interventions will be more effective in the following higher risk subgroups: older age; non-HPV related cancer sites; prior surgery; higher radiation dose; chemotherapy (yes); and, prophylactic feeding tube insertion (yes).

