The randomization of participants will be stratified by participating site using a centralized, automated and concealed process conducted by the Data Coordinating Center (DCC). Participants and therapy providers will not be blinded; however, clinical raters and data analysts will be blinded to the study arm to minimize bias. Eligible patients will be randomized in a 1:2:2 allocation to RE-ACTIVE (Arm 1, *n* = 190) and each of the PRO-ACTIVE arms (Arms 2 and 3, *n* = 381 per group). All patients will be followed to 12 months post-RT. The main intention to treat analysis will compare duration of feeding tube dependence post-RT. The study schemata is shown in Fig. 1.

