#### Sub-group analyses (heterogeneous treatment effects, HTEs)

Acknowledging that certain groups may benefit substantially while others may benefit far less, exploratory heterogeneous treatment effect (HTE) analyses are planned (Aim 3). The goal of the HTE analyses is to explore if there are subgroups for whom swallowing interventions have varied impact. For hypothesis-generating analyses, HTEs will be assessed by testing the treatment arm by subgroup interaction. Analyses are planned according to two potential sources of HTE [34]: the patient and provider**.** For parsimony, a likelihood ratio test will examine proposed HTEs simultaneously. Irrespective of their significance, the subgroup effects will be reported (with 95% confidence intervals) to be assessed in terms of clinical significance.

We have identified several participant subgroups for whom differences in treatment response or swallowing outcomes may exist. Preliminary data suggest superior swallowing outcomes in younger patients [10], those with HPV-associated cancers [68–70] those with no prior surgery [68], those who receive lower doses of RT [10], those who avoid chemotherapy [68, 71] and who avoid prophylactic feeding tube placement [9]. Each of these classifications will be examined as relevant subgroups in the exploratory HTE analysis, as justified below:

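### The primary model's fixed covariate list omits feeding tube in situ at baseline and so gives up some precision; separately, the sentence on adjusting for symptoms during RT matches no stated model

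*Protocol article*

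**What the plan says.** **Covariates.** Under Statistical analysis, Primary endpoint, days of tube use are analysed by multiple linear regression with a named set of covariates: "The meaningful variables we will include in the regression model are: age (as a continuous variable); HPV status (oropharyngeal site vs all others", then surgery, chemotherapy and radiation dose, ending with "facility (as a categorical variable to account for practice variation across the eleven sites". Nothing suggests that the list is open. It has no feeding-tube term and no symptom term.

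**Feeding tube at entry.** The section on the PRO-ACTIVE arms states that "patients with feeding tube in situ at baseline will not be excluded, but will be tracked in the trial database". Table 1 schedules the tube questionnaire, the adapted PSS-HN (which asks about feeding tube use) and the medical history at baseline. The medical history includes tube insertion and removal dates.

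**Prognostic standing.** Aims and hypotheses lists the Aim 3 factors as "age, tumor site, prior surgery, radiation dose, chemotherapy use, and prophylactic feeding tube use". The section on sub-group analyses cites preliminary data of better swallowing outcomes in several groups, among them those "who avoid prophylactic feeding tube placement".

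**Balance by design.** From the Overview of trial design: "The randomization of participants will be stratified by participating site". No other stratification factor is given.

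**Symptoms.** The MDASI-HN entry under Secondary outcomes says that the instrument "will be used to understand and adjust for symptoms such as mouth sores, pain, or dry mouth, that make eating challenging during RT". It also describes symptom burden as both a secondary outcome and a possible confounder that may affect adherence. The Secondary endpoints analysis adjusts continuous outcomes for their own baseline value only.

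**The concern.** The endpoint counts days of feeding tube use, and some patients enter with a tube already in place. Whether a tube is there at the start is an obvious candidate predictor. The protocol itself lists prophylactic tube beside five other factors, all of which enter the model, and gives no reason for leaving this one out. Because randomisation is stratified by site alone, tube status is not balanced by design between a control group of 180 and a combined group of 722 evaluable patients.

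At stake is efficiency. The section on sample size justifies the regression by the gain from adjusting for variables related to the mean response. Leaving out one that the protocol names as related gives up part of that gain, in a comparison with little spare power.

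The symptom sentence raises a different question. Randomisation precedes RT (operationally up to RT treatment day 3), and MDASI-HN is collected at weeks 2, 4 and 6. Symptoms during RT therefore arise largely after randomisation and may be changed by the assigned arm; Aim 2 hypothesises better secondary outcomes, symptom burden among them, at 3 and 12 months. Such a variable is not a confounder of the randomised comparison. Adjusting an arm comparison for it would remove whatever part of the effect runs through symptoms.

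**Working it through.** **1. Reproduce the stated power.** Inputs from Sample size calculation: 190, 381 and 381 enrolled; 5% attrition; two-sided alpha 0.05; effects of 0.23 SD (Hyp 1.1) and 0.21 SD (Hyp 1.2).

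- Attrition: 190 × 0.95 = 180.5 and 381 × 0.95 = 361.95, matching 180 and 361.
- Hyp 1.1: standard error in SD units = √(1/180 + 1/722) = 0.0833. Power = Φ(0.23/0.0833 − 1.96) = 78.8%. Detectable effect at 80% power = (1.96 + 0.84) × 0.0833 = 0.233 SD.
- Hyp 1.2: standard error = √(2/361) = 0.0744. Power = Φ(0.21/0.0744 − 1.96) = 80.5%. Detectable effect = 0.209 SD.

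Both agree with the stated 80% within rounding of the effect size. Neither uses a covariate, so the omission does not make the sample size wrong.

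**2. Compare the two lists.**

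| Aim 3 factor | Term in primary model |
|---|---|
| Age | Yes, continuous |
| Tumour site | Yes, as HPV status (oropharyngeal or other) |
| Prior surgery | Yes |
| Radiation dose | Yes, continuous |
| Chemotherapy | Yes |
| Prophylactic feeding tube | **No** |

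**3. Gain from adding the term.** If baseline tube explains a share R² of the residual variance, the SD is multiplied by √(1 − R²). The documents give no R², so the values below are assumptions.

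| Assumed R² | Power, Hyp 1.1 at 0.23 SD | Detectable effect, Hyp 1.1 | Power, Hyp 1.2 at 0.21 SD |
|---|---|---|---|
| 0 | 78.8% | 0.233 SD | 80.5% |
| 0.02 | 79.6% | 0.231 SD | 81.3% |
| 0.05 | 80.9% | 0.228 SD | 82.5% |
| 0.10 | 82.9% | 0.221 SD | 84.5% |
| 0.20 | 87.0% | 0.209 SD | 88.4% |

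The R² = 0 row treats the listed covariates as explaining nothing. If they already lift power, the gain in points is somewhat smaller.

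**4. What such R² values imply.** For a yes/no variable with prevalence p and a difference of D within-group SDs, R² = v/(1 + v) with v = p(1 − p)D². With p = 0.10 and D = 0.5, v = 0.0225 and R² = 0.022. With p = 0.30 and D = 1.0, v = 0.21 and R² = 0.174. Both p and D are assumed.

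**5. Chance imbalance.** The SD of the difference in tube prevalence between 180 and 722 patients is √(p(1 − p)) × 0.0833: 2.5 percentage points at an assumed prevalence of 10%, and 3.8 points at 30%.

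**6. The symptom sentence against the analysis sections.** The MDASI-HN entry announces adjustment but names no outcome and no model. The primary model has no symptom term, and the secondary analyses adjust only for the baseline measure. The announced adjustment therefore has no place in any model described. If it did enter an arm comparison, and a quarter or a half of a 0.23 SD effect ran through symptoms (assumed shares), the model would target 0.23 × 0.75 = 0.173 SD or 0.23 × 0.50 = 0.115 SD instead of 0.23 SD.

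**The case against.** The strongest defence is that leaving out a baseline covariate is a choice about efficiency, not an error. Randomisation protects the comparison whether or not the term is included, and the sample size was set on an unadjusted t-test. That is right, and it limits the point to precision.

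A reader might go further and treat chance imbalance as bias. With an assumed prevalence of 20% to 30%, 60 to 100 extra days of tube use and an SD of 100 days, a typical imbalance of 3.3 to 3.8 points shifts the estimate by 2.0 to 3.8 days. The documents do not support calling this bias. It is sampling error, already contained in a standard error of 100 × 0.0833 = 8.3 days on the same assumption. Nor is it a second harm on top of lost precision.

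A reader might also infer that baseline tube is the covariate closest to the endpoint. The protocol does not say so, and some features weaken the link: a tube not used for feeds is disregarded, days count only from the end of RT, and entrants have at most mild dysphagia, so a tube at entry may be precautionary and unused. Facility, chemotherapy and dose may already carry part of the information. The cited preliminary evidence concerns swallowing outcomes and prophylactic placement, not tube duration by baseline status. The true R² may therefore lie at the low end of the range. What survives is that the protocol treats the tube as prognostic and leaves it alone out of the model.

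On symptoms, the tempting reading is that the trial plans an analysis that would bias the ITT effect. It does not: no stated model has a symptom term, and the sentence sits in an instrument description that ends on adherence. What stands is an unreconciled statement.

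**Conclusion.** The point holds as a modest, inexpensive improvement and one clarification of wording. The primary covariate list gives a term to five of the six factors that the protocol names as prognostic and leaves out the feeding tube, though baseline status is recorded and randomisation does not balance it. The cost is about 1 to 8 points of power for Hyp 1.1 from a base of 78.8%, and a similar amount for Hyp 1.2 from 80.5%, if the tube explains 2% to 20% of residual variance. That range is assumed; the documents give neither the prevalence of tubes at entry nor their relation to later use. The treatment estimate is not biased and the sample size stands.

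The sentence on symptoms conflicts with the analysis sections only in wording. It deserves correction because, taken literally in an arm comparison, it would replace the ITT effect with a different quantity.

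**What to change.** - **Primary endpoint section:** add feeding tube in situ at randomisation (yes/no) to the covariate list, for both Hyp 1.1 and Hyp 1.2.
- **Aims and sub-group sections:** define the prophylactic-tube subgroup by that same pre-randomisation value. Patients and therapy providers are not blinded, so a definition that counted later placement could depend on the arm.
- **MDASI-HN entry:** state that arm comparisons adjust only for the baseline MDASI-HN score, where they adjust for MDASI-HN at all, and that symptoms during RT serve only descriptive or adherence analyses.

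The cost is one covariate from data already collected at baseline and a few sentences in the protocol and the analysis plan, best settled before any unblinded data are seen. Sample size and data collection do not change.
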